### Participants

Inclusion: Children aged 10–14, meeting the following criteria: either a clinical diagnosis of ADHD or rated by school staff or school psychologist to have impairing difficulties with inattention, hyperactivity and impulsivity, affecting the child’s school attendance. Included schools are either, schools for children with special needs or municipal schools with special educational programmes for children diagnosed with either ADHD or severe and impairing difficulties of hyperactivity, inattention and impulsivity. If the child receives pharmacological treatment for ADHD, the treatment should not be changed (dosage, timing, class of drug), during the study period.

Exclusion: Children with visual impairment, current psychotic symptoms, suicidal ideations or behaviour are excluded from the study.

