### Procedures

The participating schools identify, which children are eligible to enrol in the study. Participating children are not randomized, but included either to an intervention group or to a waiting list control group, as they are identified. Waiting list control children are recruited from schools that agree to participate in the study, but will not be part of the intervention until after study period. The children in the waiting list control group have the same characteristics as the children in the intervention group, but are not practicing target-shooting sport during the study period. Parents of all eligible children receive verbal and written information about the intervention, following the guidelines of the National Committee on Health Research Ethics. Upon parental consent, the teacher informs and provides written information to the child. The written information will be read out loud and explained to the child. Background information (including diagnosis, use of medication and participation in leisure time activities) are provided by parents one week prior to the intervention, three months into the intervention and 6 months post intervention. ADHD-RS-IV, SDQ, and KIDSCREEN-27 questionnaires are collected one week prior to the intervention. Data, from the waiting list control group, will be collected at the same time. Questionnaires will be distributed to parents and teachers. The children will fill out the questionnaire (Kidscreen-27) and complete the computer test (Qb Test) during regular school hours. A research assistant will carry out the Qb Test at the participating schools.

The multiple case study, combining interviews and observations, is nested in the quantitative survey adding substantial in-depth information. Children, parents, teachers and shooting instructors will be interviewed during the intervention. The interviews will mainly focus on experiences with the intervention and changes in quality of life and wellbeing for the children. Interviews with the children, teachers and parents will be carried out either at the school or at the child’s home address. Interviews with shooting instructors will take place in the local shooting associations. The first author will conduct and record all interviews.

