### Sample size and statistical analyses

Sample size calculations are based on the following parameters: The total score of the first 18 items of ADHD-RS-IV is the primary outcome measurement. In a validation study of a Danish clinical sample of 10–17-year-old boys with ADHD, the mean total-score was 32.3 (standard deviation (SD) 10.2) [27]. With an effect of the intervention on this outcome with a 25% reduction in the total score (=24.2) and with an expected SD of 15.2), a power of 80%, 1:1 allocation in the two groups, two-sided testing and a significance level of 5%, a total sample of 78 is required. In an evaluation of the sport project preceding this study [15] the dropout rate from participation in target shooting sport was below 15%. Following these parameters and a more conservative expected dropout at 20% it is estimated that there should be 50 children enrolled in each group. The following online statistics programme has been used for the calculation: http://www.quantitativeskills.com/sisa/calculations/samsize.htm. The primary and secondary outcomes measured for both groups, pre- and post-intervention will be analysed using linear mixed-effects models (random coefficient models and multilevel models). With the mixed effects model approach, all available data will be used and intention-to-treat analyses applied. A thematic analysis [26] will be made separately for each case, followed by an analysis across all cases to investigate common themes and patterns [17]. The number of cases enrolled will depend on when data-saturation is reached.

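### The waiting-list and intervention groups are asserted to be alike although nothing described secures it, and the stated pre/post model names no adjustment for differences in change between them

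*Protocol article*

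**What the plan says.** Under Procedures, the protocol article states that "Participating children are not randomized, but included either to an intervention group or to a waiting list control group, as they are identified". On the source of the controls it says: "Waiting list control children are recruited from schools that agree to participate in the study, but will not be part of the intervention until after" the study period ends. It then states as a fact that "The children in the waiting list control group have the same characteristics as the children in the intervention group", the only difference being that the controls do not shoot during the study.

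Under Participants, a child may enter with "either a clinical diagnosis of ADHD or rated by school staff or school psychologist to have impairing difficulties", from a special-needs school or from a special programme in a municipal school. A child may be medicated or not; for those on medication, "the treatment should not be changed (dosage, timing, class of drug), during the study period".

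Under Procedures again, the relevant data are gathered: "Background information (including diagnosis, use of medication and participation in leisure time activities) are provided by parents one week prior to the intervention" and later, and "ADHD-RS-IV, SDQ, and KIDSCREEN-27 questionnaires are collected one week prior to the intervention", with control data collected at the same time.

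Under Sample size and statistical analyses: "The primary and secondary outcomes measured for both groups, pre- and post-intervention will be analysed using linear mixed-effects models". The section adds that these are random coefficient and multilevel models, that all available data are used, and that the analysis is by intention to treat. It names no covariate and does not write out the treatment contrast.

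**The concern.** Randomisation is what would entitle a plan to expect the same characteristics in both groups. This design has none, and no substitute is described. Sharing eligibility criteria is weaker than sharing characteristics. When the criteria admit diagnosed and undiagnosed children, medicated and unmedicated children, and two kinds of school, two sets of schools can meet them all and still differ in mix.

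This matters because the treatment effect is read from a comparison of the groups over six months. If diagnosed, medicated or more severely affected children, or children in one kind of school, tend to change differently over that time, an uneven mix produces a difference with no contribution from shooting. If covariates were instead chosen after the data were seen, on an unblinded teacher rating, that would add a second weakness.

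**Working it through.** **The passages side by side**

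1. Allocation: not randomised, and controls come from schools that start later. Group therefore follows school.
2. Eligibility: diagnosis or staff rating; special school or municipal special programme; medicated or not. Case mix can vary between schools.
3. Steps to secure balance: none described. The rule on stable medication limits change in treatment during the study. It does not limit imbalance in who is medicated at the start.
4. Analysis: a mixed model on pre and post scores with no covariate named.

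**What the pre/post model does and does not remove**

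The article does not spell out the contrast, so take the natural reading, group by time. With two occasions and complete data it estimates

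effect = (post − pre) in the intervention group − (post − pre) in the control group.

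- A stable difference in level cancels.
- A difference in underlying change stays in full. If a characteristic goes with D points of extra change and its prevalence differs by p between groups, the bias is p × D.
- A covariate entered only as a main effect is the same at both occasions and cancels too, so it does not remove this bias. It needs an interaction with time.
- A school random effect deals with correlation, not with confounding between schools.

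**Illustrative size**

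Inputs from the article: planned effect 32.3 − 24.2 = 8.1 points (8.1/32.3 = 25%, as stated); SD 15.2 (sample size) or 10.2 (reference sample); 50 enrolled per group less 20% = 40 completers. Both SDs are shown because the stated total of 78 does not follow from SD 15.2, which gives 112. That mismatch is a separate matter and is not used here.

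Assumptions, since the article gives no values: difference in underlying change b = 2, 3 or 4 points; pre-post correlation r = 0.5 or 0.7; true effect zero; school clustering ignored because the number of schools is not given.

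As a share of the planned effect: 2/8.1 = 25%, 3/8.1 = 37%, 4/8.1 = 49%.

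SE of the contrast = SD × √(2(1 − r)) × √(2/40).

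Rejection rate = 1 − Φ(1.96 − b/SE) + Φ(−1.96 − b/SE).

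| SD | r | SE | b = 2 | b = 3 | b = 4 |
|---|---|---|---|---|---|
| 15.2 | 0.5 | 3.40 | 9% | 14% | 22% |
| 15.2 | 0.7 | 2.63 | 12% | 21% | 33% |
| 10.2 | 0.5 | 2.28 | 14% | 26% | 42% |
| 10.2 | 0.7 | 1.77 | 21% | 40% | 62% |

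The nominal rate is 5%. On another scale, a shift of 0.25 SD is 0.25 × 15.2 = 3.8 points, or 3.8/8.1 = 47% of the planned effect. At SD 10.2 it is 2.55 points, or 31%.

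**Why two models are worth reporting**

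Let the baseline means differ by B with no true effect.

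- If the difference is stable, the change contrast gives 0, and a baseline-adjusted model of the post score gives B − rB = (1 − r)B.
- If the difference arose from selection on the observed score, the post difference is rB. The change contrast then gives −(1 − r)B, which is regression to the mean, and the baseline-adjusted model gives 0.

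For B = 3, the bias in whichever model is wrong is 1.5 points at r = 0.5 and 0.9 at r = 0.7. The article does not say which case applies.

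**The case against.** The strongest reply is that this is a condensed article. Covariate lists and baseline tables are commonly left to the full protocol or analysis plan, and collecting diagnosis and medication fits with planned adjustment. The article is also open about the lack of randomisation, holds medication constant, confines recruitment to special schools and programmes, and says larger randomised trials are needed if the result is positive. The comparability sentence could be a loose way of saying that the same eligibility rules apply to both groups.

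Much of this stands. Four stronger readings are tempting, and the article does not support them:

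- **That the model adjusts for nothing.** This would be inferred from silence. The article names a model class and neither lists nor excludes covariates.
- **That baseline scores are ignored.** They enter the model as the pre-intervention measurement.
- **That staff chose children knowing their school's group.** The article does not say when each school's group was settled.
- **That a baseline-adjusted model must replace the group-by-time contrast.** In intact groups neither dominates, as the working shows.

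The reply does not reach the comparability sentence itself. That is a positive claim in the text, not an omission, and the later call for randomised trials does not withdraw it.

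**Conclusion.** The point holds in this form. The article claims comparability that nothing it describes can deliver, and the analysis it states, taken as it stands, leaves differential change by diagnosis, medication, school type or starting severity inside the effect estimate. Confounding of this kind is the main threat to a non-randomised comparison.

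The documents do not show that the groups are in fact unbalanced, or in which direction any bias would run. Unequal regression to the mean is possible but not demonstrated, since eligibility sets no score cut-off for either group. The figures of 25% to 49% of the planned effect, and the inflated rejection rates, rest entirely on assumed bias sizes and correlations. They show that modest differences in underlying change would matter at this sample size and are not estimates for this trial.

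**What to change.** 1. Replace the comparability sentence with a statement that the same eligibility criteria apply to both groups and that baseline characteristics will be reported by group.
2. Before outcomes by group are examined, pre-specify the primary contrast as group by time for the teacher-rated ADHD-RS-IV total, adjusted for ADHD diagnosis, baseline medication, age and school type. Give each an interaction with time so that it can affect change. Include school as a level, and do not constrain the baseline means to be equal.
3. As a sensitivity analysis, model the post-intervention score on group with adjustment for the baseline score and the same covariates. State that the two models rest on different assumptions in non-equivalent groups, and report both.
4. Acknowledge residual confounding in the conclusion.

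The cost is analysis-plan wording and a few degrees of freedom: four covariates, each with a main effect and a time interaction, make eight coefficients if each is a single term. Diagnosis and medication are already collected, and age and school type are part of eligibility. One limit remains: if a school type occurs in only one group, adjustment cannot separate the two, and the baseline table should make that visible. No change to recruitment or allocation is needed.

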### Sample size and statistical analyses

Sample size calculations are based on the following parameters: The total score of the first 18 items of ADHD-RS-IV is the primary outcome measurement. In a validation study of a Danish clinical sample of 10–17-year-old boys with ADHD, the mean total-score was 32.3 (standard deviation (SD) 10.2) [27]. With an effect of the intervention on this outcome with a 25% reduction in the total score (=24.2) and with an expected SD of 15.2), a power of 80%, 1:1 allocation in the two groups, two-sided testing and a significance level of 5%, a total sample of 78 is required. In an evaluation of the sport project preceding this study [15] the dropout rate from participation in target shooting sport was below 15%. Following these parameters and a more conservative expected dropout at 20% it is estimated that there should be 50 children enrolled in each group. The following online statistics programme has been used for the calculation: http://www.quantitativeskills.com/sisa/calculations/samsize.htm. The primary and secondary outcomes measured for both groups, pre- and post-intervention will be analysed using linear mixed-effects models (random coefficient models and multilevel models). With the mixed effects model approach, all available data will be used and intention-to-treat analyses applied. A thematic analysis [26] will be made separately for each case, followed by an analysis across all cases to investigate common themes and patterns [17]. The number of cases enrolled will depend on when data-saturation is reached.

## Discussion

Adapting the environment to provide a clear and concise structure, in regards to routines, time and space, is recognized as a helpful educational and method for children with ADHD symptoms [28, 29]. Developing a well-structured environment provides the child with an opportunity to improve self-control, regarding impulsivity and attention [29]. Children with ADHD tend to benefit from having their own protected physical space, when involved in focused activities. They also tend to benefit from having a designated adult close by, to provide support in retaining focus [29]. However, such beneficial effects are only possible, if the children find the activity interesting and not as a punishment and also, children with ADHD tend to be motivated by activities with an immediate feedback [24, 29, 30]. Earmuffs are often recommended for children with ADHD, to make a sound barrier, which eliminates auditory disturbances [28, 29].

All these above-mentioned elements are present, when practicing target-shooting sports in local shooting associations in Denmark. There are clearly defined, non-negotiable rules, a clear structure and a predictable setting. This makes target-shooting sport an activity, which is easy to understand and practice, also for children with ADHD. At the shooting range, participants are allocated an individual separate cubicle. Children are supervised at all times by a designated adult instructor, who stays in close proximity of the child. During practice the instructor intends to establish a good connection with the individual child, who benefits from support and recognition. When aiming and shooting, participants receive immediate feedback, as to whether they hit bulls-eye. Preliminary findings from the initial sport project indicate, that participating children enjoys target-shooting sport, show on-going motivation, while at the same time increasing their ability to stay focussed on hitting the target [15]. The unique characteristics of target-shooting sport, combined with theoretical knowledge on the subject of children with ADHD and preliminary project experience in the field, indicate beneficial effects of practising target-shooting sport in local Danish shooting associations in children with symptoms of inattentiveness, hyperactivity and impulsivity.

At present, no research has investigated the effects of target shooting sports in children with impairing symptoms of inattentiveness, hyperactivity and impulsivity. If found effective in this open trial, larger randomized controlled trials of this intervention are needed. If such trials provide evidence that practising target-shooting sports has beneficial effects, it may become a relevant supplement to the current interventions available for children with ADHD. This may aid the development and adaption of other leisure activities and physical activities and increase the possibilities of participation for children with ADHD. The results may further add to the continued search for effective and motivating non-pharmacological interventions that may help and support children with ADHD.
